# Conventional Versus Underwater Endoscopic Mucosal Resection for Superficial Non-Ampullary Duodenal Epithelial Tumors ≤ 20 mm: Study Protocol for a Multicenter Randomized Controlled Trial (D-CURE Trial)

**DOI:** 10.3390/mps9010030

**Published:** 2026-02-23

**Keywords:** conventional endoscopic mucosal resection, underwater endoscopic mucosal resection, sporadic non-ampullary duodenal epithelial tumors, non-inferiority randomized controlled trial, recurrence-free survival rate

## Abstract

**Background:** Underwater endoscopic mucosal resection (UEMR) is a relatively new treatment method for sporadic non-ampullary duodenal epithelial tumors (SNADETs), and its usefulness has been reported for SNADETs ≤ 20 mm. However, its effectiveness and safety compared with conventional endoscopic mucosal resection (CEMR) remain controversial. This study aims to assess the treatment outcomes and evaluate the beneficial effects and safety of UEMR for SNADETs ≤ 20 mm. **Methods:** This is an open-label, multicenter collaborative, non-inferiority randomized controlled trial with two parallel groups conducted across 40 institutions in Japan. The study subjects will be patients with SNADETs ≤ 20 mm. A total of 320 patients will be randomized to either the CEMR or UEMR group in a 1:1 allocation ratio. The primary endpoint is the 1-year recurrence-free survival rate, defined as the number of cases with no recurrence of SNADET or death from any cause within one year of EMR. The secondary endpoints include the *en bloc* resection rate, histological complete resection rate, adverse events, technical success rate, total procedure time, resection time, mucosal closure time, complete mucosal closure rate, complete mucosal closure rate with standard clips, 1-year duodenum preservation survival rate, and device cost. **Discussion:** This multicenter, open-label, randomized controlled trial (RCT) with 320 subjects aims to determine whether the 1-year recurrence-free survival rate of underwater endoscopic resection is not inferior to that of conventional endoscopic mucosal resection for SNADETs ≤ 20 mm. If the efficacy and safety of UEMR are proven in this RCT, it is expected to be recognized as the standard treatment for SNADETs ≤ 20 mm. Owing to the absence of submucosal injection, UEMR is a simpler and more cost-effective technique compared to CEMR and is anticipated to become the primary method of EMR.

## 1. Background

Sporadic non-ampullary duodenal epithelial tumors (SNADETs), which seldom metastasize to lymph nodes, are generally considered more suitable for less-invasive endoscopic resection (ER) than for surgery [1]. However, there are challenges associated with ER for SNADETs owing to the specific anatomical features of the duodenum, such as thin walls, exposure to bile and pancreatic juices, and poor endoscopic maneuverability. Although conventional endoscopic mucosal resection (CEMR) is more widely adopted owing to its simplicity and safety, complication rates are higher in the duodenal ER than in the ER of other digestive tracts owing to these factors [2].

There is a lack of comparative studies between CEMR and other ER methods, leading to the absence of established standard treatments for SNADETs ≤ 20 mm [3]. Notably, the American Society for Gastrointestinal Endoscopy guidelines do not specifically mention the standard treatments [4]. In contrast, the European Society of Gastrointestinal Endoscopy guidelines established CEMR as the standard treatment, irrespective of the tumor size [5]. Because *en bloc* resection of SNADETs > 20 mm is often difficult using EMR, endoscopic submucosal dissection (ESD) is performed in Japan. Before starting this trial, the community reached a consensus to set CEMR as the standard ER for SNADETs ≤ 20 mm. However, preoperative biopsy scars and the presence of Brunner’s glands in the submucosal layer can cause inadequate mucosal elevation through submucosal injection in CEMR, leading to piecemeal resection or conversion to ESD [6]. Additionally, piecemeal resection increases the risk of recurrence, which may require surgical intervention if recurrence occurs, indicating the need for improvement in CEMR [7,8,9,10].

Recently, the feasibility of underwater EMR (UEMR) as a method to overcome the difficulties associated with CEMR has been reported [11]. UEMR is an ER technique that uses the phenomenon of lesions floating toward the lumen by filling the duodenal lumen with water or saline, resembling the effect of a submucosal injection. Because UEMR does not require submucosal injection, it can address the difficulty of resection owing to insufficient mucosal elevation, a common issue in CEMR. Additionally, UEMR offers the advantage of stable snaring without snare slippage owing to insufficient mucosal elevation, even in flat lesions. Furthermore, owing to the villous mucosa of the duodenum and thin proper muscle, submucosal injection is relatively challenging compared with injection into other gastrointestinal tracts. The performance of UEMR for SNADETs ≤ 20 mm has been evaluated in a multicenter study, where the results indicated an *en bloc* resection rate of 89.9%, a histological complete *en bloc* resection rate of 66.9%, an intraoperative perforation rate of 0%, a postoperative bleeding rate of 1.2%, a delayed perforation rate of 0%, and a one-year recurrence-free survival rate of 97.2%, suggesting its safety and efficacy [12]. The reported histologically complete *en bloc* resection rate is lower for UEMR than for CEMR [2,13,14,15,16], which may be associated with local recurrence after UEMR. However, it is important to note that the single-arm trial was subject to selection bias, and the treatment outcomes of the CEMR used as the historical control may differ from the current data. Additionally, it is unclear whether the trial data can be externally validated [3]. Therefore, it is necessary to demonstrate the non-inferiority of the local recurrence rate of UEMR using direct comparison with CEMR.

The D-CURE trial aims to assess the treatment outcomes and evaluate the beneficial effects and safety of UEMR for SNADETs ≤ 20 mm.

## 2. Methods and Analysis

### 2.1. Study Settings

The D-CURE trial is an open-label, multicenter, collaborative, non-inferiority randomized controlled trial (RCT) with two parallel groups, conducted across 40 institutions in Japan. The control arm will include patients who undergo CEMR, whereas the study arm will include patients who undergo UEMR. Figure 1 shows the flowchart of the D-CURE trial. The trial protocol was developed in accordance with the Standard Protocol Items: Recommendations for Interventional Trials (SPIRIT) guidelines [17]. The SPIRIT flow diagram is shown in Figure 2.

### 2.2. Approvals

The study protocol was approved by the certified review board of Tohoku University (No. 34158; 22 November 2023). The trial was registered in the University Hospital Medical Information Network (UMIN) Clinical Trials Registry (UMIN000052778; 17 November 2023).

### 2.3. Patient Selection

Patients who meet all the inclusion criteria and none of the exclusion criteria will be considered eligible for enrollment.

**Figure 1 mps-09-00030-f001:**
[figure not shown]
Flowchart of the D-CURE trial. CEMR, conventional endoscopic mucosal resection; UEMR, underwater endoscopic mucosal resection.

**Figure 2 mps-09-00030-f002:**
[figure not shown]
Time schedule for the D-CURE trial. CEMR, conventional endoscopic mucosal resection; UEMR, underwater endoscopic mucosal resection.

#### 2.3.1. Inclusion Criteria

Endoscopically diagnosed adenoma, adenocarcinoma, or histologically confirmed adenoma or adenocarcinoma through preoperative biopsy.The lesion has a longitudinal diameter of 20 mm or less.The estimated tumor depth is limited to the mucosa.The lesion is located in the duodenal bulb, descending part, or horizontal part, without invasion into the major or minor papilla.The lesion is non-pedunculated.Scheduled for endoscopic treatment for a single lesion.No history of gastrectomy or duodenectomy.Age at the time of registration ranges from 18 years to 85 years.Eastern Cooperative Oncology Group Performance Status is 0, 1, or 2.Has received adequate explanation regarding trial participation and has provided written consent.

#### 2.3.2. Exclusion Criteria

Diagnosed with familial adenomatous polyposis (FAP).Presents with systemic infections requiring systemic treatment.Pregnant or breastfeeding women.Psychiatric disorders, psychiatric symptoms, or dementia that would hinder participation in the trial.Complicated by unstable angina (occurrence within the last three weeks or exacerbation of angina) or a history of myocardial infarction within the past six months.Patients taking multiple antithrombotic drugs for whom endoscopy is recommended to be postponed according to the Japanese guidelines for gastrointestinal endoscopic treatment of patients receiving antithrombotic agents [18,19].Complicated with respiratory diseases requiring continuous oxygen therapy.Patients with a prognosis of less than 1 year.Other patients deemed inappropriate by the attending trial physician.

### 2.4. Informed Consent Procedure

The patients will be screened for eligibility by endoscopists at each institution based on the abovementioned criteria. The principal investigator or the physician in charge will obtain free and voluntary written consent from the patients after providing a full explanation of the research using explanatory documents (Supplemental Material File). Written informed consent will be obtained from all patients who wish to participate in this study. They will also be informed that they can withdraw their consent at any time.

### 2.5. Randomization

A randomization process will be conducted using a central web-based system to assign patients to either the CEMR or UEMR group in a 1:1 allocation ratio. For random allocation, a minimization method will be used, incorporating four allocation adjustment factors that may influence the treatment outcomes of EMR. Allocation concealment will be ensured using a central web-based system, through which treatment assignments will be generated only after patient registration and confirmation of eligibility. Investigators and endoscopists will not have access to the allocation sequence in advance and will be unable to predict upcoming assignments.

#### Randomization Adjustment Factors and Their Selected Reasons for This Selection

Institution

In a multicenter collaborative study, variations among enrolled patients and subtle differences in treatment methods between facilities are anticipated to potentially influence EMR outcomes.

2.Pretreatment biopsy (presence vs. absence)

Pretreatment biopsies are often performed to confirm histology. However, 24.6% of patients with preoperative biopsies may encounter non-lifting signs after submucosal injection owing to biopsy-induced fibrosis [6]. Therefore, preoperative biopsies can affect the treatment outcomes of EMR.

3.Tumor size (<10 mm vs. ≥10 mm)

As the tumor size increases, CEMR and UEMR show lower *en bloc* resection rates [15]. For lesions measuring 5–9 mm, the *en bloc* resection rates were 95.8% and 93.3% for CEMR and UEMR, respectively. For lesions measuring 10–14 mm, the *en bloc* resection rates were 91.3% and 81.5% for CEMR and UEMR, respectively. For lesions measuring 15–19 mm, the *en bloc* resection rates were 74.4% and 62.0% for CEMR and UEMR, respectively. The maximum tumor diameter in this trial is 20 mm; therefore, a cut-off value of 10 mm was set.

4.Tumor location (bulb vs. other portions)

Gastric-type mucinous lesions are often found in the duodenal bulb, whereas intestinal-type mucinous lesions typically present in the descending part of the duodenum towards the anal side, particularly below the major papilla [20,21,22]. Gastric-type and intestinal-type adenocarcinomas differ in the frequency of submucosal invasion, which likely affects the long-term effectiveness of EMR.

### 2.6. Blinding

Owing to the study design, blinding endoscopists is not feasible. Endoscopists will be aware of the allocated groups at the time of treatment. Patients will also be informed of their assigned groups. Pathological assessment will be performed by pathologists who are blinded to treatment allocation.

### 2.7. Interventions

The protocol treatment will be initiated within 90 days of registration. Each patient with SNADET will be treated using the assigned endoscopic procedure during hospitalization. Only one target lesion will be treated per patient. For CEMR and UEMR in this trial, only physicians who meet the following conditions will be allowed to participate in the treatment as surgeons: (1) CEMR: Experience with CEMR in any organ in over 20 cases and (2) UEMR: Experience with UEMR in any organ in over 20 cases. Intraoperative sedation should follow the guidelines for sedation in endoscopic treatment supervised by the Japan Gastroenterological Endoscopy Society [23]. Treatment under general anesthesia is also permitted. During EMR, the patient’s status should be monitored using blood pressure, electrocardiography, and oxygen saturation.

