### 2.9. Outcomes

#### 2.9.1. Primary Endpoint (For Non-Inferiority)

The primary endpoint is the 1-year recurrence-free survival rate (1-year RFS), defined as the number of cases where no recurrence of SNADETs or death from any cause is observed within one year (12 ± 2 months) after EMR, with all treated cases as the denominator. Cases in which follow-up EGD cannot be performed because of tracking difficulties will be considered non-recurrent.

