### 2.12. Data Collection and Management

After obtaining written consent from the patients, the investigators will reconfirm that the cases meet all inclusion criteria and do not meet any exclusion criteria. Subsequently, investigators who have been pre-registered in the D-CURE Electronic Data Capture (EDC) system will enter anonymized data into the web-based EDC system of the UMIN Internet Data and Information Center for Medical Research (UMIN INDICE). Changes made in the EDC will be recorded in a log, including information on who made the changes and when. The EDC system and associated databases will be secured and protected with specific passwords. The collected data will be stored online. However, if patients request data deletion after withdrawing their consent, their data will be deleted.

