### 2.13. Planned Statistical Analyses

In this trial, the primary analysis will be conducted for the primary endpoint, the 1-year RFS, and this will be the final analysis. The analysis will be conducted within a year from the end date of final data collection of the registered cases by an independent biostatistician separate from the research physicians. Given the short planned registration and observation periods after protocol treatment, an interim analysis aimed at early termination will not be conducted.

The full analysis set (FAS) will consist of all enrolled patients who are randomized to the study arm, excluding some patients for the following reasons: violation of the eligibility/exclusion criteria, erroneous enrollment, no available data after randomization (e.g., withdrawal of consent), and failure to undergo EMR for SNADET. Cases in which the treatment protocol is changed or discontinued will be included in the FAS. The per-protocol set (PPS), a subset of the FAS, will exclude FAS cases with the following violations: incomplete protocol treatment and other serious protocol violations (e.g., treatment for SNADET exceeding 20 mm). The safety analysis set will include patients enrolled in this study whose treatment protocol is initiated and whose clinical course is followed for up to 28 days after the EMR. Cases in which protocol treatment has not been initiated will not be included in the safety analysis set.

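### The primary analysis set drops randomised patients who, after open allocation, are found ineligible, withdraw or have no EMR, and no stated analysis would show an imbalance between arms

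*Protocol article*

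**What the plan says.** - **Allocation.** Section 2.5: "treatment assignments will be generated only after patient registration and confirmation of eligibility". Section 2.12 places the eligibility check after consent and before data entry: "the investigators will reconfirm that the cases meet all inclusion criteria and do not meet any exclusion criteria".
- **Delay.** Section 2.7: "The protocol treatment will be initiated within 90 days of registration".
- **Open arms.** Section 2.6: "Endoscopists will be aware of the allocated groups at the time of treatment", and "Patients will also be informed of their assigned groups".
- **Primary population.** Section 2.13.1 bases the efficacy analysis on the FAS. Section 2.13 removes from it randomised patients with eligibility violations or erroneous enrolment, and also those with "no available data after randomization (e.g., withdrawal of consent), and failure to undergo EMR for SNADET".
- **Retained cases.** Section 2.13 also says: "Cases in which the treatment protocol is changed or discontinued will be included in the FAS".
- **Denominator.** Section 2.9.1 defines 1-year recurrence-free survival (RFS) "with all treated cases as the denominator".

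**The concern.** A 90-day scheduling window is ordinary, and an open-label design is unavoidable here. The difficulty is their combination with a primary population whose membership is settled after allocation. Between allocation and EMR, a patient can withdraw, be re-judged ineligible, or end up without EMR, and each of these can be influenced by the known arm. If the patients who leave differ in recurrence risk and the loss differs between arms, the FAS no longer compares the groups that were randomised.

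The Discussion defends the open-label design by saying that the endpoint does not depend on the endoscopist's judgement. That may hold for the outcome, but not for who enters the denominator. With few events expected, a handful of patients can matter to a non-inferiority conclusion.

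**Working it through.** **1. Who leaves the FAS, from Sections 2.7.5 and 2.13**

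| Patient after allocation | In the FAS? |
|---|---|
| Allocated EMR started, then converted | Yes (treatment changed or discontinued) |
| Given the other EMR method | Yes (has had EMR; treatment changed) |
| Taken directly to ESD or surgery | Unclear: treatment was changed, but there was no EMR |
| Re-judged ineligible | No. For a lesion over 20 mm it is unclear, because Section 2.13 names its treatment as a per-protocol exclusion |
| Withdraws with no data | No |
| No lesion treatment | No |

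**2. Could a stated analysis reveal the loss?** The per-protocol set is a subset of the FAS. Both missing-EGD analyses in Section 2.13.3 start from the FAS. The stricter-margin analyses in the Discussion change the margin, not the population. No analysis of all randomised patients is described.

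**3. The plan's own figures (Section 2.10).** The inputs are RFS 97% in both arms, margin 5 points, one-sided 0.05 and power 80%. Per arm:

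n = (1.645 + 0.842)² × 2 × 0.97 × 0.03 / 0.05² ≈ 144

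This gives 288 in total, and 288 / 0.90 = 320. Both figures reproduce. The allowance is 32 patients, 16 per arm.

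**4. Illustration.** From the plan: 160 per arm, CEMR event rate 3% (4.8 events), margin 5 points, one-sided 0.05. Assumed: true UEMR event rate 8% (12.8 events), so that UEMR lies exactly on the margin; k patients leave before EMR, from UEMR only, each with event risk r had they been treated as allocated. The observed UEMR event rate is then (12.8 − k·r) / (160 − k).

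For k = 5 and r = 0.30: (12.8 − 1.5) / 155 = 11.3 / 155 = 7.29%, an apparent difference of 4.29 points instead of 5.

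The chance of falsely declaring non-inferiority comes from exact enumeration of an unpooled Wald test. The article does not name its test, so this too is an assumption.

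| Loss before EMR | False non-inferiority |
|---|---|
| None | 6.1% |
| 5 UEMR at 30% risk | 11.1% |
| 3 to 8 UEMR at 20–40% risk | 7.4% to 19.7% |
| 5 UEMR at average risk (8%) | 6.7% |
| 5 UEMR and 2 CEMR, all at 30% | 8.7% |
| 5 UEMR and 5 CEMR, all at 30% | 5.8% |

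The 6.1% in the first row is the Wald test's own excess over 5% and has nothing to do with exclusions. A normal approximation with a 5.0% baseline agrees in pattern: 8 UEMR leavers at 20–40% risk give 8.2% to 17.4%.

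**5. What an all-randomised analysis recovers.** Suppose the 5 leavers are kept with their actual outcomes after some other treatment, at an assumed event risk of 0–3%. The UEMR rate is then 11.3 / 160 = 7.06% to 11.45 / 160 = 7.16%, and false non-inferiority is 12.1% to 11.3%, no better than 11.1%. Counting the 5 as events gives 16.3 / 160 = 10.19%, a difference of 7.19 points. Observed outcomes alone therefore do not undo the modelled bias; the second version bounds it from the other side.

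**The case against.** **Most switched patients stay in.** A reader might infer that any hard lesion can be moved out of the analysis by going to another method. Section 2.13 does not support that. It keeps changed or discontinued treatment, and its exclusion refers to not having EMR at all, not to missing the allocated EMR. This stands, and it narrows the point to the unclear and excluded rows of the first table.

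**The direction is not known.** A reader might infer that the loss must favour UEMR, because Section 2.5 reports lower en bloc rates for it (62.0% against 74.4% at 15–19 mm) and the Background reports lower histologically complete resection. The same sections also give reasons for reluctance in the CEMR arm: biopsy scars and Brunner's glands impair lifting, with non-lifting in 24.6% after biopsy. Loss of hard lesions from CEMR would work against non-inferiority. This stands.

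**Timing of disclosure.** The article does not say when sites see the allocation, only that it is generated after registration and that endoscopists know it when treating. Release at registration is the natural reading of a central web system, but it is an inference. The point needs only that the arm is known before the patient's inclusion is settled, which is already possible at the treatment session.

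**The size is assumed.** No passage gives the number or risk of such patients, and balanced loss removes the effect. This stands; the figures show sensitivity and are not a forecast.

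**Left to the analysis plan.** Reporting losses by arm commonly is. The FAS and the denominator, however, are fixed in this article.

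**Conclusion.** The concern holds in a limited form. The primary FAS and its denominator depend on decisions and events after an open allocation, and no stated analysis would expose an arm-dependent loss. Those affected are patients re-judged ineligible, withdrawn without data or given no EMR; patients taken directly to ESD or surgery cannot be classified from the text.

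The bias could run either way. If UEMR is truly on the margin and only UEMR loses 3 to 8 patients at 20–40% risk, false non-inferiority rises from about 6% to 7–20%. With balanced or average-risk loss it stays near 6–7%. The documents do not show that such loss has occurred or will occur. The 90-day window is not itself an error, and the sample size is unaffected.

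**What to change.** Amend Sections 2.13, 2.13.1 and 2.13.3:

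1. Allow exclusion for eligibility only on data recorded before randomisation, judged blind to arm and outcome. State how a lesion found to exceed 20 mm only at treatment is classified.
2. State that patients taken directly to any other resection method stay in the FAS in their allocated arm.
3. Prespecify a sensitivity analysis of the primary endpoint in all eligible randomised patients by allocated arm, once with observed outcomes and once with no-EMR patients counted as events. Define the time origin for patients without EMR. Require the non-inferiority conclusion to be read alongside both versions, with pre-EMR losses reported by arm and reason.

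The cost is an amendment, a little more analysis and possibly a less favourable result. The version that counts leavers as events is deliberately severe. If UEMR is truly at 97% and 5 of its patients have no EMR, its event rate becomes (155 × 0.03 + 5) / 160 = 6.0%, a 3.0-point deficit created by the rule alone. It should serve as a bound, not as a replacement for the primary analysis.

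Releasing the allocation on the day of EMR would shorten the exposed interval, but it is optional: randomisation began in December 2023 (Trial Status), so the change would reach only later patients.
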